### Sample size

Sample size estimates are based on the numbers of participants needed to detect differences in proportions of participants in intervention and control groups:

1) Participating in physical activity (defined as reaching the national target recommendations of five sessions of 30 minutes or more of at least moderate activity per week).

2) Self perceived health as measured by the EQ-5D index, from which meanQALY scores and the incremental cost-effectiveness ratio will be calculated.

Under individual randomisation, sample size calculations for a small effect size (0.3) [61] equivalent to a mean difference of 0.05 in the EQ-5D index in general community samples requires 176 participants per study group [62]. Published evidence of participants in a cluster randomised trial of physical activity promotion showed the proportions of participants achieving the same recommended targets for physical activity to be 14.6% (intervention subjects) vs. 4.9% (control subjects) [63]. A total of 215 participants in each study group are required to detect this difference between study groups with 90% power (5% 2-sided significance). Current plans seek a 1% increase in the number of people achieving the physical activity target of five sessions of 30 minutes or more of at least moderate activity per week, year on year [1].

Data from 24 general practices in the British Regional Heart study suggested that an intra-class correlation coefficient (ICC) not exceeding 0.02 was appropriate for physical activity outcomes among middle aged men, but this study aimed to represent the full range of cardiovascular disease prevalence across Britain and the range would probably be less in the proposed study as it is less geographically dispersed [64]. Also ICCs collected for a range of variables in primary care settings have typically averaged 0.01 [65].

Based on an intra class correlation coefficient of 0.01 the design effect would be 1.31, because 32 participants will provide data per practice (see next paragraph). If 215 participants per arm are required (before allowing for attrition) for an individually randomised design (90% power, 5% 2-sided significance), 282 per arm would be required for the clustered design. Allowing for 30% attrition, this equates to 403 per arm. The sample size is based on detecting differences between each intervention (exercise programme) and the control arm, and there is unlikely to be enough power to detect modest differences in outcome between the two intervention arms.

Assuming an average practice size of 6000 patients, 15% (900) of whom are aged 65 and over [66] and a random 1 in 2 sample (ratio will vary according to the practice size) of patients are approached to take part in the study, 600 patients aged 65 and over would be approached. Assuming that approximately 45 of these patients per practice agree to participate, and allowing for an attrition rate of 30%, outcome data would be obtained on 32 participants per practice.

It is expected that all or most patients in each practice will be invited to join the trial. In larger than average practices, however where the patient list is very large, a stratified random sample of 600 patients will be drawn. Response rates from each practice will be recorded.

### Randomisation

Due to the relatively small number of practices in the trial, minimisation will be used to allocate practices to treatment arms to ensure maximum balance [67]. After all participants from a practice have been recruited, their practices will be individually allocated to a study arm by the London co-ordinating centre. Practices will be given an identification number and treatments will be assigned, by the senior statistician for the trial, using computer generated random number tables, embedded in a computer programme for minimisation. The variables to be used in the minimisation process will be trial centre (London/Nottingham & Derby), practice size (>= median practice size/< median practice size) and the index of multiple deprivation 2007 [68] (>= median IMD2007/< median IMD2007). Minimisation will be undertaken using the MINIM program [69]. Practice recruitment and allocation will be performed concurrently in the two centres. Median practice size and IMD2007 values for the whole of England will be used as cutpoints for the minimisation process.

### Concealment of allocation

Practices are allocated to intervention or usual care only after all patients are recruited. The practices, their patients and the researchers undertaking baseline assessments are all blinded to allocation until this point.

### Blinding

It is difficult for participants to be blind in trials of exercise interventions, and for researchers to be blind to the allocation of participants as they will recruit participants and undertake baseline and follow up assessments. The researchers assessing outcomes are not blinded for pragmatic reasons only; the study is funded to support only enough researchers to carry our recruitment and follow-up simultaneously. However, general practices and their participants, and researchers having contact with practices and participants will not have foreknowledge of the treatment arm allocation of the practice, which will not be disclosed until after all participants within a practice have been recruited. Also, for the statistical analysis of participants' data, the statistician will be blind to the treatment arm allocation of the practices.

### Withdrawals

Participants may be withdrawn from the trial either at their own request or at the discretion of the Investigator after discussion with the chair of the trial steering committee. Participants will be made aware (via the information sheet and consent form) that withdrawal from the trial will not affect their future care, and that the data collected to date may still be used in the final analysis. Any requests to withdraw data made by individuals withdrawing from the trial will be respected. The research teams at each site will advise discontinuation of exercise intervention or withdrawal from the trial if the exercise intervention poses a hazard to the safety of a participant, or if the participant poses a hazard to the safety of another participant. Those who withdraw from the trial will not be replaced.

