#### Usual care

Participants in the usual care arm will not be offered either the OEP or FAME programmes. They will be free to participate in any other exercise as they would if they were not participating in the trial.

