### Outcome measures

The primary and secondary outcome measures have been chosen to reflect the needs of participants (e.g. functional outcomes, falls, confidence, quality of life, participant costs), of commissioners of exercise services in primary care and policy makers (e.g. physical activity, falls, NHS costs).

The primary outcome will be the proportion reaching the recommended physical activity (PA) target of at least 30 minutes of activity of moderate intensity on at least 5 days each week, measured using the CHAMPS, PASE and PHONE_FITT questionnaires. While measures will be taken at 0, 6, 12, 18 and 24 months after the intervention, our primary analysis will be of 12 month data, as this is the time when the effect of the intervention is expected to be maximal, as seen in a previous evaluation of the OEP in New Zealand [37].

The secondary outcomes will include:

(1) The direct health benefits: i.e. functional and psychological status, the rate of falls (the major safety outcome measure), the number and nature of falls, and fear of falling,

(2) Stage of change, self-efficacy for exercise and physical self-perception (self-esteem relative to the physical domain), which includes measurement of perceived importance (the degree to which participants value their physical condition, body image and physical strength) to inform predictors of exercise adherence and continuation, and participants' judgement of the value or importance of physical activity,

(3) Health - related quality of life and Quality adjusted life years (QALYs) [38],

(4) The NHS and private (participant) costs of each exercise programme, and possible cost offsets, identified from a comparison of health and social service utilisation of participants in all groups during the study period.

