In addition, demographic information, co-morbidity, medication, use of general practice and hospital and community social services will also be recorded at baseline and updated at subsequent assessments. Falls will be ascertained by self-completed fall diaries, with follow up of non-responders and telephone contact with fallers to ascertain the type of fall and any injury and health care usage that resulted.

Feedback will be sought from all exercise participants using a questionnaire which will include open questions eliciting views of the programme, reasons for drop-out, barriers to attendance and self perceptions of the benefits and disadvantages of the programmes to aid future implementation.

For the purposes of the economic analysis, the resources used in the delivery of the interventions will be collected from records kept by PSI instructors (FaME) and the research staff and peer mentors (OEP). The use of facilities and equipment, and the time spent on travel and instruction will be included and monetary costs will be assigned according to market rates.

In addition, the use of health and social care services (GP, community, outpatient, hospital admission) will be recorded for participants in all groups by means of the falls diaries. Self reported service utilisation will be verified from the primary care medical records of consenting patients after the follow up period. Costs of services will be obtained from local and national sources [60]. Health and social care costs in the exercise groups will be compared with each other and with the usual care (no exercise) group to assess the extent to which the costs of the exercise intervention may be offset by savings elsewhere in the health and social care system.

No other encouragement to continue with physical activity will be given to participants, and all potential reinforcements in the form of diaries and six monthly contracts will be given to all three arms of the trial.

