#### Follow-up data collection

Follow up assessments occur at 24 weeks after the commencement of the intervention, and at 6, 12, 18 and 24 months after the completion of the intervention for participants in both intervention arms, and at 24 weeks after randomisation and at 6, 12, 18 and 24 months after completion of the 24 week assessment in the control arm.

The 24 week functional assessment will be identical to the baseline assessment plus administration of all questionnaires described above.

Assessments at 6, 12, 18 and 24 months after completion of the intervention or after completion of the 24 week assessment in the control arm will comprise postal administration of the questionnaires described above.

The primary end-point will be the proportion reaching the recommended physical activity (PA) target of at least 30 minutes of activity of moderate intensity on at least 5 days each week, measured using the CHAMPS, PASE and PHONE_FITT questionnaires, at 12 months after intervention.

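### For two hazards that arise only or mainly in the exercise arms, site teams may advise leaving the trial as well as stopping exercise, so later falls data could be lost selectively

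*Protocol article*

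**What the plan says.** The Withdrawals section has two layers.

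- **Formal withdrawal:** "Participants may be withdrawn from the trial either at their own request or at the discretion of the Investigator after discussion with the chair". The chair meant is that of the steering committee. This applies in every arm.
- **Site advice:** "The research teams at each site will advise discontinuation of exercise intervention or withdrawal from the trial if the exercise intervention poses a hazard". Here the person at risk is the participant who exercises. A second trigger is worded "or if the participant poses a hazard to the safety of another participant". Two responses are offered for two triggers, without saying which belongs to which.

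On data after withdrawal, the section reports that participants are told "the data collected to date may still be used in the final analysis". It does not say that someone stopped for safety stays in follow-up.

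Other sections bear on this:

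- **Usual care:** "Participants in the usual care arm will not be offered either the OEP or FAME programmes".
- **Outcome measures:** the fall rate is named as the major safety outcome.
- **Ascertainment of outcomes:** "Falls will be ascertained by self-completed fall diaries, with follow up of non-responders".
- **Follow-up data collection:** the assessments 6 to 24 months after the intervention "will comprise postal administration of the questionnaires described above".
- **Statistical methods:** missing outcomes are multiply imputed under missing at random (MAR), with baseline value, arm and compliance among the predictors. The one stated departure from that assumption counts people who do not report exercise levels as non-exercisers.

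**The concern.** Stopping a treatment and leaving a study are different events, and the sentence offers them as alternatives for the same hazard. The hazard is tied to allocation. Exercise can be hazardous as a trial programme only in OEP and FaME, and one participant endangers another mainly where participants meet, in FaME classes. Any follow-up lost by this route would therefore be lost almost entirely from the exercise arms.

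Leaving the trial adds nothing to safety beyond stopping the exercise, because diaries and postal questionnaires carry no exercise exposure. It does remove the later falls of people for whom exercise was judged risky, whose experience a safety comparison should keep. If their fall rate stays raised in a way the imputation does not capture, the exercise arms look safer than they are. The sensitivity analysis for non-reporters protects the primary outcome but says nothing about falls.

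The full analysis set also requires one post-baseline assessment of the primary outcome, and the first is at 24 weeks. Someone withdrawn from the trial during the 24-week programme would normally have none, and the article does not say whether imputation reaches beyond that set.

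**Working it through.** **The plan's own figures.** The concern disputes none of them, and they reproduce. A two-proportion calculation for 14.6% against 4.9% with 90% power, 5% two-sided and continuity correction gives 215 per arm. The design effect is 1 + (32 − 1) × 0.01 = 1.31, so 215 × 1.31 = 281.65, or 282. Allowing for attrition, 282 / 0.70 = 402.9, or 403 per arm.

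**Assumptions for the falls calculation.** The documents give no safety-withdrawal rate and no fall rate for those withdrawn, so these are assumed:

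- T = 128 weeks of diaries (24-week programme plus 24 months, taken as 104 weeks).
- w = week of withdrawal, 12 (also 4 and 24).
- p = share of an exercise arm withdrawn, 2% or 5%. Of 403 this is 403 × 0.02 ≈ 8 or 403 × 0.05 ≈ 20 people.
- Fall rate of the remaining participants = 1.
- k = rate of the withdrawn while exercising, 2 or 3; k′ = their rate after stopping.
- c = rate imputed for them after withdrawal; d = k′ − c, the excess that imputation misses.

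**Formulas.**

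- True arm rate = [(1 − p)T + p(kw + k′(T − w))] / T
- Estimated arm rate = [(1 − p)T + p(kw + c(T − w))] / T
- Share of time after withdrawal at week 12 = 116/128 = 0.906

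**Break-even.** How large must d be for the arm's fall rate to be understated by 5%? With c = 1, setting estimated/true = 0.95 gives

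d = [1 + p(k − 1)w/T] × (1/0.95 − 1) / [p(T − w)/T]

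- p = 2%, k = 2: 1.001875 × 0.05263 / 0.018125 = 2.91
- p = 5%, k = 2: 1.0046875 × 0.05263 / 0.0453125 = 1.17

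Taking k = 3 leaves these almost unchanged. Across weeks 4 to 24 the range is 2.7–3.3 at 2% and 1.1–1.3 at 5%. So at 2% withdrawn, the missed excess must be nearly three times the others' rate, which means falling about 3.9 times as often in total when c = 1.

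**Estimated/true rate when the excess persists in full (k′ = k, w = 12).**

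| Withdrawn, k | Imputation captures none of the excess | Half | All |
|---|---|---|---|
| 2%, 2 | 0.982 | 0.991 | 1.000 |
| 2%, 3 | 0.965 | 0.983 | 1.000 |
| 5%, 2 | 0.957 | 0.978 | 1.000 |
| 5%, 3 | 0.918 | 0.959 | 1.000 |

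For example, at 2% and k = 2 with none captured, the true rate is 1.020 and the estimated rate 1.0019, a ratio of 0.982. If the excess risk ends when exercise stops and imputation assigns the others' rate (k′ = c = 1), every ratio is 1.000. Adjustment for baseline values is not modelled.

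**The case against.** The strongest reply is that nothing in the text requires loss of follow-up. Stopping exercise is listed first, the conjunction permits it alone, and site teams only advise. Formal withdrawal needs the participant's request, or the Investigator's discretion after discussion with the steering committee chair. Elsewhere the protocol treats not exercising as compatible with staying in: those who do none of a programme are protocol violations, the CACE analysis needs outcomes from non-compliers, and diary non-responders are followed up. The phrase about data collected to date tells participants what happens if they leave; it is not a rule for those who only stop exercising. The 24-week functional assessment includes physical tests, so follow-up is not wholly free of exertion.

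On size, few safety withdrawals are likely. Eligibility excludes people with three or more falls or uncontrolled conditions, and the Risks section reports no adverse effects in earlier evaluations. A hazard need not be a fall hazard. Compliance is a named imputation predictor, so capturing none of the excess is the worst case. Adverse events are followed until resolution or stabilisation, or until the intervention is shown not to be the cause.

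Most of this stands as a limit on size and certainty. It does not remove the point. The provisions for non-compliers do not cancel an instruction under which a site may advise someone to leave the trial. The functional assessment could be skipped on its own. Nor is this detail left to a fuller document: it is a conduct rule that the article states, and no analysis plan can restore diaries that were never collected.

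**Conclusion.** The concern holds, as a minor point. The rule permits, but does not require, follow-up to end for a safety reason that arises only or mainly in the exercise arms, with no gain in safety over stopping exercise. Any resulting bias in falls would favour exercise, but only if those withdrawn keep a higher fall rate after stopping and the imputation predictors miss it. Its size cannot be established from the documents. Under the assumed ranges the understatement runs from nothing to about 8%, and the upper end needs 5% withdrawn, three times the fall rate persisting in full, and imputation that captures none of it. The likely effect is small. The primary outcome is better protected, by imputation and the non-exerciser sensitivity analysis.

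**What to change.** In the Withdrawals section, make discontinuation of the exercise intervention the only response that site teams advise for either trigger, and delete trial withdrawal from that sentence. Add that these participants continue fall diaries, adverse event follow-up and postal questionnaires, and are analysed in their allocated arm, unless they withdraw consent to data collection. Leave unchanged the participant's right to withdraw, the Investigator's discretion after discussion with the steering committee chair, and the clinical grounds for stopping exercise.

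The cost is one wording change and a line in site training. The downside is more diaries and questionnaires to send and chase, for about 8 to 20 people per exercise arm under the assumed 2–5%. That work would fall to a research team whose capacity the Blinding section already describes as limited.

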#### Contamination

Usual care arm participants may be disappointed and seek their own way of increasing physical activity, but the falls and service use diaries and the 6 monthly reviews will capture this information.

### Statistical methods

Characteristics of participants and practices will be compared descriptively at baseline. Comparisons between treatment arms will be made using random effects models to allow for clustering between practices. Linear regression models will be used for continuous outcome variables, logistic models for binary outcome variables (in particular the primary endpoint, namely attainment of recommended exercise level at 12 months after the intervention), and Poisson or negative binomial models for data on rate of falls. The assumptions for using each model will be checked and analyses adjusted accordingly. All analyses will be undertaken, adjusted (a) for variables used for minimisation (centre, deprivation and practice size), (b) for baseline values of the outcome measure, and (c) for baseline variables which differ to a clinically significant extent between groups. Differential effects of the intervention by age, sex and baseline activity levels will be assessed for the primary outcome measures by adding terms for the interaction between age, sex and baseline activity levels and treatment arm to the regression models.

Multilevel models will be applied to take account of clustering at the practice level (applicable to all arms of the study) and practitioner effects which will apply to differing extents in the OEP arm (due to the effectiveness of different PSIs) and FaME arm (due to the effectiveness of different PMs). Analyses as recommended by Roberts [70] and Walwyn and Roberts [71] (2009) will be applied for this purpose.

While the primary endpoint will be attainment of recommended exercise levels at 12 months, we will investigate the profile of exercise attainment at all time points (0, 6, 12, 18 and 24 months post intervention). We will carry out repeated measures analysis using generalised estimating equations which account for the intra-participant dependency of the repeated measures. In particular we will investigate evidence for differences in effect of the interventions at the different time points.

As the study consists of two intervention arms and one control arm, primary analysis will consist of comparing each intervention group with the control group. No formal adjustment of p-values will be made, since the sample size has been specifically designed to test each intervention separately.

The economic analysis will adopt standard techniques of economic appraisal [72]. The measure of effectiveness will be mean differences in QALY scores at the end of follow up after adjustment for baseline values, estimated in an analysis of covariance. If statistically significant differences between groups are found, incremental cost effectiveness ratios will be calculated to show the extra cost incurred per QALY gained. Comparisons will be conducted between the usual care group and each type of exercise programme, and between the two interventions, using group means of follow-up QALY values after adjusting for baseline levels. The impact of uncertainties in the estimation of costs and outcome variables will be explored using one way and probabilistic sensitivity analysis. Bootstrap methods will be used to represent uncertainty of estimates, either for constructing confidence intervals or probability curves.

Sensitivity analyses will investigate the cost-effectiveness of the interventions for people with different levels of physical activity, health status and health related quality of life at baseline. Secondary cost-effectiveness analyses will be conducted using physical activity and other outcomes as the measures of effectiveness.

Missing outcome data will be assumed to be "missing at random" (MAR), conditional on key predictors of "missingness" (in particular baseline values of the response variable, treatment arm, and measures of compliance post randomisation) Multiple imputation of outcome variables will be carried out using these predictors of "missingness" [73]. A further sensitivity analysis will be carried out where all who do not report their exercise levels will be assumed to be non-exercisers.

The full analysis set will comprise all randomised participants for whom one post-baseline assessment of the primary outcome measure is available. The per-protocol set will comprise all randomised participants who are deemed to have no protocol violations. CACE analysis will be carried out [74].); this seeks to estimate the difference between compliers in the intervention groups with those who would have complied in the non-intervention group. The safety set will be all randomised participants who undertake at least one OEP session or FaME class.

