## Design/Methods

A 3 arm parallel design cluster controlled trial using minimisation for allocation at the level of general practice in two centres (London and Nottingham/Derby), comparing community-centre based group exercise programme (FaME), with a home based exercise programme and walking plan (OEP) and with usual care. There will be two years' follow-up to determine the impact, acceptability and adherence to the programme, longer term continuation of exercise and cost-effectiveness. The CONSORT diagram [35] summarises the design (Fig 1).

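### The repeated-measures GEE and the QALY analysis are specified without practice, the unit of randomisation, which is inconsistent with the protocol's own general rule on clustering

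*Protocol article*

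**What the plan says.** Practice is the unit of allocation: the Design/Methods section describes a cluster trial "using minimisation for allocation at the level of general practice in two centres". The Sample size section builds this into its arithmetic: "Based on an intra class correlation coefficient of 0.01 the design effect would be 1.31", with 32 participants per practice providing data.

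Statistical methods gives two general statements on clustering. The first says that arms will be compared with random effects models that allow for practice. The second says that multilevel models will handle practice-level clustering in every arm.

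The same section then specifies two analyses in their own words:

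- **Time course (0, 6, 12, 18 and 24 months; secondary objective 4):** "We will carry out repeated measures analysis using generalised estimating equations which account for the intra-participant dependency of the repeated measures". The next sentence says that the particular interest is whether intervention effects differ between time points.
- **Economic analysis:** effectiveness is measured by "mean differences in QALY scores at the end of follow up after adjustment for baseline values, estimated in an analysis of covariance". ICERs are calculated if the group differences are statistically significant. Uncertainty is covered thus: "Bootstrap methods will be used to represent uncertainty of estimates".

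Neither description mentions practice.

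**The concern.** The GEE sentence names the dependency it handles, and that dependency is within the participant. A GEE whose clusters are participants treats people from the same practice as independent. The practice random effects in the general rule cannot simply be carried over, because a GEE is a marginal model and contains none. Practice enters only if it is made the clustering unit or the variance is corrected in some other way.

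The QALY analysis has the same gap. An ordinary analysis of covariance, or a bootstrap that resamples individuals, ignores the level at which arms were assigned.

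Two results are at stake. One is the time profile, a stated secondary objective. The other is the economic result: the Background section lists the relative cost-effectiveness of the two programmes among the primary hypotheses, and QALY significance decides whether ICERs are produced at all. A test that rejects too often would open that gate too often, and intervals from an individual-level bootstrap would be too narrow.

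**Working it through.** **Inputs from the Sample size section.** ICC 0.01 for planning; 0.02 as the ceiling from the British survey of middle-aged men; 32 participants with data per practice; about 45 recruits per practice; 30% attrition; proportions 14.6% and 4.9%; two-sided 5%; 90% power.

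**Reproducing the plan's figures**
- The two-proportion formula gives 195 per group with a pooled variance and 215 with a continuity correction. The plan states 215, so it matches the corrected version.
- Design effect = 1 + (32 − 1) × 0.01 = 1.31, as stated.
- 215 × 1.31 = 281.65, so 282; 282 / 0.7 = 402.9, so 403. Both match.
- 403 / 45 = 8.96, so about 9 practices per arm.

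**Arm effect at one visit if practice is ignored**

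The true standard error is √DE times the reported one, and the actual level of a nominal 5% test is 2 × [1 − Φ(1.96 / √DE)].
- ICC 0.01: DE 1.31, √1.31 = 1.145, level 8.7%.
- ICC 0.02: DE = 1 + 31 × 0.02 = 1.62, √1.62 = 1.273, level 12.4%.
- ICC 0.005 (assumed, for a low value): DE 1.155, level 6.8%.
- Unequal practice sizes (assumed coefficient of variation 0.2 to 0.4): 8.8% to 9.3% at ICC 0.01, and 12.7% to 13.5% at ICC 0.02.

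**Simulation check**

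9 practices per arm, 32 people each, five visits, no true effect, continuous outcome, assumed within-person correlation 0.5, standard errors that respect the participant only, 4,000 runs. Monte Carlo error is about 0.3 to 0.5 percentage points: √(0.05 × 0.95 / 4000) = 0.34% and √(0.12 × 0.88 / 4000) = 0.51%.

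| ICC | Correlation of practice effect across visits | Arm effect at one visit | Arm-by-time (last minus first visit) |
|---|---|---|---|
| 0.01 | 1.0 | 8.9% | 5.0% |
| 0.01 | 0.8 | 8.6% | 6.5% |
| 0.02 | 1.0 | 12.5% | 5.1% |
| 0.02 | 0.8 | 12.1% | 8.1% |

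A practice effect that is constant over time cancels from a difference between visits, so the arm-by-time test then keeps its level. It drifts upward only as far as practice effects change between visits.

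**Effect averaged over five visits**

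With within-person correlation r, the variance of a person's mean is v = (1 + 4r) / 5, and DE = 1 + 31 × ICC / v. For r between 0.3 and 0.7 (assumed) and a constant practice effect, the level is 9.9% to 13.3% at ICC 0.01 and 14.6% to 20.7% at ICC 0.02. The protocol does not name this quantity as a target.

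**The case against.** The best defence is that nothing in the protocol says practice will be dropped. The two general statements on clustering are unrestricted, and the GEE sentence follows them and may only be naming the extra dependency that repeated visits bring. A GEE clustered on practice also accounts for correlation within a person, so the wording is compatible with a valid analysis. A journal article may also leave the clustering level of a secondary model, and the resampling scheme, to a fuller document.

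Much of this stands. A reader might infer that practice is definitely ignored, and the text does not support that. What remains is that the article does specify these analyses, names one dependency for the GEE and gives the QALY model without practice. The general rule is phrased in terms of a model class to which the GEE does not belong.

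A reader might also object that an unweighted GEE needs data missing completely at random. The document answers this. "Missing outcome data will be assumed to be" missing at random, and the same paragraph plans multiple imputation of outcomes, plus a sensitivity analysis that counts non-reporters as non-exercisers.

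Three limits on the size are fair:
- No ICC for QALYs is given.
- The Sample size section expects less between-practice variation in this trial than in the survey behind the 0.02 ceiling.
- All analyses are to be adjusted for centre, deprivation, practice size and baseline values, which may lower the residual ICC. The calculations make no allowance for this.

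**Conclusion.** The point holds as an inconsistency to be resolved. The general clustering rule and the specific descriptions of the GEE and the QALY analysis do not fit together, and an analyst who followed the specific sentences would ignore the unit of randomisation.

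In that case, an arm effect at a single visit would have a false positive rate of about 8.7% at the plan's own ICC and practice size, and 12.4% at ICC 0.02. These figures assume equal practice sizes and no reduction of the ICC through covariates. The simulation used a continuous outcome, whereas exercise attainment is binary. For QALYs the figures also assume an ICC similar to those quoted for other variables.

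It is tempting to put one inflated range, such as 9-13%, on all these tests. The documents do not support that. The arm-by-time contrast that the protocol singles out stays at about 5-8%. The higher values for a time-averaged effect depend on assumed correlations and an unnamed target. Every figure is conditional on practice being left out. The primary 12-month comparison comes under the random effects rule and is unaffected.

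**What to change.** State how the general rule applies to each analysis:

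1. **Time course.** Keep the GEE, but make practice the clustering unit. Its robust variance then covers dependence both within participants and within practices. Use a small-sample-corrected variance, since there are only about 9 practices per arm, and fit the model to the multiply imputed data already planned. Keeping the GEE preserves population-averaged odds ratios; a three-level logistic model would replace them with conditional ones.
2. **QALYs and costs.** Include a practice random effect in both models.
3. **Bootstrap.** Resample practices rather than treating individuals as independent.

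This changes analysis wording only. No extra data or participants are needed, and the design effect is already in the sample size. The downside is slightly wider intervals than an analysis ignoring practice would give: about 14% wider for a single-visit arm effect at ICC 0.01 (√1.31 = 1.145), plus a little for the small-sample correction.
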